## Abstract

**Background:**

Dementia represents a key health issue for older adults, with negative consequences on psycho-social and functional status. Treatments that counteract cognitive deficits in mild cognitive impairment (MCI) are needed to prevent or delay it.

**Aim:**

To describe the experimental protocol of the STRENGTH Project. This study investigates a multimodal intervention in older adults with MCI to improve cognitive, functional, biochemical and psycho-social aspects.

**Methods:**

The prospective randomised controlled trial will enrol 300 subjects with MCI (age ≥ 60 years). Participants will be randomly assigned to: (a) the experimental group, which will undergo sessions of adapted tango, music therapy, engagement in social activities, cognitive intervention and psycho-education for 6 months or (b) the control group, which will receive psycho-education and advice on healthy lifestyle for 6 months. All outcomes will be analysed before intervention (baseline), immediately after termination (follow-up 1), after 6 months (follow-up 2) and after 2 years (follow-up 3).

**Discussion:**

We expect that the findings of this multidisciplinary study will be useful to optimize clinical and psycho-social interventions for improving cognitive and functional status of subjects with MCI.

**Conclusions:**

This project could have a meaningful impact on National Health Systems by providing clues on multidisciplinary management of older adults affected by cognitive decline to prevent dementia.

## Introduction

Dementia is a chronic and progressive syndrome that affects 5–8% of general population aged 60 years or more [1]. Dementia damages memory, thinking and behaviour and has negative consequences on psycho-social functioning. Treatments that counteract cognitive deficits in mild cognitive impairment (MCI), a translational state between age-associated cognitive decline and diagnosed dementia, are needed to prevent or delay it.

Previous studies evidenced that currently available pharmacological therapies are not effective [2], while the use of psycho-social interventions in association with cognitive training and physical activity (PA) has been recognized to improve functional capabilities of older adults, thus positively acting on the onset of neurological diseases [3]. Management of cardiovascular and lifestyle-related risk factors is particularly promising [4]. Healthy lifestyle, engagement in regular moderate PA, and involvement in social recreational activities may have protective effects both on mental functions and on risk of dementia [5–7]. Data from our previous "My Mind Project" (Grant no. 154/GR-2009–1584108) showed that subjects affected by MCI had lower level of PA and social participation than age-matched healthy controls and highlighted the potential negative consequences of this situation on psychological conditions and functional status [8]. These findings suggest the necessity to develop multimodal interventions for elderly people with compromised cognition [9]. Indeed, according to the literature [3, 10], single-domain trials did not yield long-term effects and, consequently, are not really effective for dementia prevention. Thus, in the STRENGTH Project, we decided to study the effect of a multimodal intervention that associates PA (i.e., adapted tango for non-demented elderly people), cognitive stimulation, music therapy and other psycho-social treatments.

PA programmes based on dance were proved to promote in the elderly population the preservation of functional mobility, the improvement of cognitive processes, mood status and well-being and reduction in the fear of falling [11–13]. In particular, a randomised, controlled trial conducted in Italy evidenced specific psycho-social and physical benefits in applying PA based on dance, thanks to the improved balance capability and the reduced risk of falling in the enrolled elders [14]. Nevertheless, more studies regarding dance interventions in the Italian elderly population are needed [11].

Adapted tango was previously tested by other authors, in subjects with different cognitive status, as it was proven to be feasible and safe for improving mobility, physical functions, spatial cognition and memory with maintenance of the positive achievements for 3 months after the end of the intervention [15, 16]. Moreover, it seems that tango is a particularly innovative approach because of its low PA impact and its effectiveness in promoting positive emotional state and alleviating psychological distress, such as anxiety and depression status in elderly people [17–19]. Depression, anxiety and psychological stress are often observed in MCI subjects due to their consciousness of the cognitive decline; moreover, their subjective memory complaints could intensify the deficit perception worsening their performances [9].

Given this background, the aim of our study is to ameliorate cognition, physical functioning and quality of life in MCI patients, with a potential positive impact on cognitive decline and dementia onset prevention/delay.

## Methods

### Study design

The STRENGTH Project is a prospective randomised controlled trial for the assessment of the effects of a multimodal intervention (i.e., adapted tango, music therapy, engagement in social activities, cognitive stimulation, and psycho-education for 6 months) in subjects with MCI. The study uses a multidisciplinary approach, has a 3-year duration and includes 3 follow-up phases, as indicated in Fig. 1.

**Fig. 1 Fig1:**
[figure not shown]
Flowchart of strength project

#### Specific aim 1

To study the effect of the multimodal intervention on cognitive performances, functional status, and mobility in MCI subjects by objectively measured parameters (baseline vs. follow-up 1, follow-up 2 and follow-up 3). Mobility (i.e., the ability of a subject to move in his/her environment) is often compromised in elderly people as a consequence of falls and other injuries and this could cause disability and reduced social engagement. The identification of approaches that might prevent motor–cognitive impairment would be a pivotal advancement in the correct management of aging people. Mobility will be evaluated by means of balance, walking test and gait speed; motor–cognitive function, defined as a process of coordination of movements finalized to a particular motor goal, will be measured by means of visual–spatial memory task.

The longitudinal monitoring of cognitive decline and dementia onset will also be implemented (follow-up 2 and follow-up 3).

#### Specific aim 2

To study the effect of the intervention on psycho-social aspects (e.g., psychological well-being, perceived stress, quality of life, metacognition and mood status), lifestyle characteristics and social network (baseline vs. follow-up 1, follow-up 2 and follow-up 3).

#### Specific aim 3

To study the effect of the intervention on specific biomarkers (baseline vs. follow-up 1, follow-up 2 and follow-up 3).

#### Experimental design aim 1

Neuropsychological as well as cognitive and clinical assessment, including cardiovascular, anthropometric, and functional evaluation (e.g., blood pressure, body mass index, ultrasound heart examination through standard echocardiogram, 6-min walk test, gait speed, Berg Balance Scale, handgrip strength, Physical Activity Scale for the Elderly, basic activities of daily living and instrumental activities of daily living) will be carried out (Table 1).

**Table 1 Tab1:** Clinical, functional, and neuropsychological assessment

Instruments
*Cognitive assessment*
Clinical Dementia Rating Scale—CDR [20]
Memory Complaint Questionnaire—MAC-Q [21]
Montreal cognitive assessment—MoCA [22]
Mini mental state examination—MMSE [23]
Rey auditory verbal learning test—RAVLT [24]
Phonological verbal fluency—PVF [24]
Supra-span of Corsi [25]
Semantic verbal fluency—SVF [26]
Attentive matrices [26]
Trail making test A−B—TMT A–B [27]
*Psychological assessment*
Depression Anxiety Stress Scale—DASS [28, 29]
Geriatric Depression Scale-15—GDS-15 [30]
Psychological Well-Being Scales—PWB [31, 32]
SF-36 (36 health survey) [33]
*Functional assessment*
Basic activities of daily living—ADL [34]
Instrumental activities of daily living—IADL [35]
Berg Balance Scale—BBS [36]
6-min walking test—6MWT [37]
*Social network*
Lubben Social Network Scale—LSNS [38]
*Lifestyle characteristics and physical activity*
Physical Activity Scale for the Elderly—PASE [39]
Lifestyle Questionnaire

#### Experimental design aim 2

Enrolled subjects will undergo a detailed protocol of tests and questionnaires to evaluate the following aspects: psychological well-being, perceived stress, quality of life, metacognition, mood status, lifestyle characteristics and social network (Table 1) [20–39].

#### Experimental design aim 3

The following parameters will be evaluated (details are reported in Fig. 2):BDNF and ceruloplasmin protein amounts in plasma and their mRNA expression in peripheral blood monuclear cells (PBMC), as the role of peripheral leukocyte dysfunctions in Alzheimer’s disease (AD) development [40, 41] is well known;mRNA expression in PBMC of 84 key genes involved in AD physiopathology (i.e., beta-amyloid generation, oligomerization, clearance, and degradation; cytoskeleton regulators; synaptic formation; lipid metabolism; apoptosis; cell cycle; cell signalling molecules; transcriptional regulation; oxidative stress; proteases and protease inhibitors);plasma copper, zinc, and other important micronutrients;a panel of the most common laboratory parameters.

**Fig. 2 Fig2:**
[figure not shown]
The panel represents all the biomarkers that will be analysed in the STRENGTH Project for each tissue (i.e., whole blood, plasma, and peripheral blood mononuclear cells). *RBC* red blood cells, *WBC* white blood cells, *MCV* mean corpuscular volume, *PT* prothrombin time, *PTT* partial thromboplastin time, *BDNF* brain-derived neurotrophic factor, *ALT* alanine amino transferase, *AST* aspartate amino transferase, *BUN* blood urea nitrogen, *e-GFR* estimated glomerular filtration rate, *CKD-EPI* chronic kidney disease epidemiology collaboration, *HDL* high-density lipoprotein, *LDL* low-density lipoprotein, *Cu* copper, *Zn* Zinc, *Se* selenium, *Fe* iron, *Ca* calcium, *Mg* magnesium, *Na* sodium, *K* potassium, *AD* Alzheimer’s Disease

### Recruitment and screening phase

The project started on 1 August 2019 and will last until 31 July 2022. The protocol was approved by the local ethics committee (Bioethics Advisory Committee of IRCCS INRCA, Ancona, Italy; code no. 18006). Three hundred community-dwelling older adults (age ≥ 60 years) with diagnosis of MCI will be enrolled in the Evaluation of dementia’s disease Unit of IRCCS INRCA Hospital in Fermo. MCI will be diagnosed by an extended neuropsychological, clinical and functional evaluation, as well as by neuroimaging and laboratory tests according to diagnostic guidelines [42]. The subjects’ screening will be performed during routine clinical visits applying specific inclusion/exclusion criteria as explicated below. Written informed consent will be obtained from all subjects.

### Randomisation

The selected subjects will be randomly allocated to the experimental group (EG, *n* = 150) or to the control group (CG, *n* = 150) using a randomisation list.

### Inclusion and exclusion criteria

The inclusion criteria comprise: (a) diagnosis of MCI according to the guidelines of the National Institute of Aging [42]; (b) age 60 years or older, (c) availability during the intervention and testing phases, (d) presence of a caregiver; (e) capability to sign the informed consent.

Exclusion criteria include: (a) presence of sensory-physical deficits that would prevent participation in the study; (b) diagnosis of dementia; (c) presence of serious medical and/or psychiatric conditions.

### Sample size calculation

It was based on the null hypothesis that proportion of “success” and “failure” of the intervention is equal in the two groups (i.e., EG and CG), such as OR = 1.

Success and failure were defined on the basis of significant variation in the primary outcomes. Considering an OR = 1.5 indicative of an effect of the intervention, a total sample of 300 subjects allows us to reach a 90% of statistical power using logistic regression at the 5% level (two tailed). Drop-out rate was set at 20%.

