#### Primary outcome: success of the intervention

The response to the intervention will be evaluated using performance in the Corsi test [25]: an increase of at least 1 point will indicate a success based on the enhancement of the spatial learning processes.

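### The stated 90% power for an odds ratio of 1.5 with 300 subjects cannot be right: a two-arm logistic regression has at most 42% power, and at most 35% after the planned 20% drop-out

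*Protocol article*

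**What the plan says.** The section on sample size calculation in the protocol article sets the null hypothesis that the "proportion of “success” and “failure” of the intervention is equal in the two groups (i.e., EG and CG), such as OR = 1". The alternative is "Considering an OR = 1.5 indicative of an effect of the intervention", and the section concludes that "a total sample of 300 subjects allows us to reach a 90% of statistical power using logistic regression at the 5% level (two tailed"). It adds "Drop-out rate was set at 20" per cent, without saying whether the power figure is before or after that loss.

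The other design features are given elsewhere in the article:

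- The Abstract says "The prospective randomised controlled trial will enrol 300 subjects with MCI".
- The Randomisation section assigns 150 to the experimental group "or to the control group (CG, *n* = 150) using a randomisation list".
- The primary outcome is binary, based on the Corsi test: "an increase of at least 1 point will indicate a success based on the enhancement of the spatial learning processes".

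No control-arm success rate is stated.

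**The concern.** With a binary outcome and two equal arms, an odds ratio of 1.5 is a modest effect. If 40% of controls succeed, it corresponds to 50% success in the experimental group. Detecting a ten-point difference near the middle of the scale with 90% power normally takes about a thousand subjects, so 300 looks far too few.

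The figure matters because it tells readers how to interpret the primary result. If true power at the target effect is below one half, this test is more likely to miss that effect than to find it. A non-significant result, presented as coming from a trial with 90% power, could then be read as evidence of no benefit when it says little either way.

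**Working it through.** **Inputs from the protocol article.** Odds ratio 1.5, two-sided 5%, logistic regression, total 300, drop-out 20% (sample size section); 150 per arm (Randomisation); binary success (primary outcome section). Evaluable subjects after loss: 300 × 0.8 = 240, or 120 per arm.

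**Input not given.** The control success rate p0. It is treated as unknown and scanned from 1% to 99%.

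**Formulas (Wald test of the log odds ratio, n per arm).**

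- p1 = 1.5·p0 / (1 − p0 + 1.5·p0)
- SE² = 1/[n·p1(1 − p1)] + 1/[n·p0(1 − p0)]
- z = ln(1.5)/SE, with ln(1.5) = 0.4055
- power = Φ(z − 1.96) + Φ(−z − 1.96)

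**Attempt to reproduce the 90%.** Take p0 = 40%, so p1 = 50%.

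- n = 150: SE² = 1/(150 × 0.25) + 1/(150 × 0.24) = 0.02667 + 0.02778 = 0.05444. SE = 0.2333, z = 1.738, power = 41.2%.
- n = 120: SE² = 0.05444 × 150/120 = 0.06806. SE = 0.2609, z = 1.554, power = 34.3%.

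| Control success | Experimental success at OR 1.5 | Power, 150 per arm | Power, 120 per arm |
|---|---|---|---|
| 10% | 14.3% | 20.5% | 17.3% |
| 20% | 27.3% | 31.5% | 26.2% |
| 30% | 39.1% | 38.2% | 31.7% |
| 40% | 50.0% | 41.2% | 34.3% |
| 45% | 55.1% | 41.6% (maximum) | 34.6% (maximum) |
| 50% | 60.0% | 41.2% | 34.3% |
| 60% | 69.2% | 38.5% | 32.0% |
| 80% | 85.7% | 25.8% | 21.6% |

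The pooled two-proportion test gives the same maxima. Simulation at a 45% control rate gave 41.7% and 33.2% for the Wald test, and 44.0% and 33.2% for the likelihood-ratio test.

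**Why no control rate helps.** Since p(1 − p) ≤ 0.25, SE² cannot be smaller than 2/(n × 0.25) = 16/N, where N is the total. For N = 300, z ≤ 0.4055/√(16/300) = 1.756, so power is at most about 42%. For N = 240, z ≤ 0.4055/√(16/240) = 1.570, so power is at most about 35%. Covariate adjustment for a conditional odds ratio of 1.5 cannot exceed this bound.

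**Sample size for 90% power.** n per arm = (1.960 + 1.282)² × [1/(p0(1 − p0)) + 1/(p1(1 − p1))] / 0.4055². At p0 = 45% this is 516.6 per arm, or about 1,033 in total. The pooled two-proportion formula gives 1,026. Allowing for 20% loss, 1,026/0.8 ≈ 1,283 would have to be enrolled.

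**Odds ratio detectable with 90% power (Wald, control rates 20% to 50%).** 2.14 to 2.36 with 300 evaluable; 2.35 to 2.60 with 240 evaluable.

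**Other readings tried.**

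- One-sided 5%: at most 54.2% (150 per arm) or 46.8% (120 per arm).
- 300 per arm: at most 69.7%.
- Continuous standardised predictor, odds ratio 1.5 per SD, 50% success: N = (1.960 + 1.282)²/(0.25 × 0.4055²) = 255.7, so 256; × 1.2 = 307. Power is 94.0% at N = 300 and 88.1% at N = 240.
- 1.5 read as a risk ratio: 86.7% to 93.8% with 150 per arm at control rates of 35% to 40%.

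Only the last two come near 90%, and neither is the stated design. A 1:1 arm indicator has variance 0.25, not 1, and the text says odds ratio throughout. That the figure came from one of these routes is conjecture, and the conclusion does not depend on it.

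**The case against.** - **The article is condensed, and the full protocol may give the control rate.** This does not help, because the result is a ceiling over all control rates. The published combination of odds ratio, total, test, significance level and power is false whatever that rate is.
- **The error may lie in the effect measure.** If 1.5 was meant as a risk ratio, power near 90% is possible at some control rates. This is a fair reason to ask the sponsor which effect was intended. But the null and the alternative are both written as odds ratios, and the paragraph would still need correction.
- **The meaning of 300 can be inferred.** The Abstract and the Randomisation section make 300 the number enrolled. What remains open is whether 90% was meant for 300 or for 240 evaluable subjects. Both are covered above.
- **The Statistical analysis section names general linear models and repeated measures ANOVA, not logistic regression.** An analysis of the Corsi score as continuous could have different power, which cannot be computed from the document. This stands as a limit: the low power found here is that of the stated calculation on the dichotomised primary outcome.
- **Restating power is not the only remedy.** A larger sample or a justified larger target effect are alternatives, and nothing in the article shows that an odds ratio above 2 is plausible. That also stands, and the choice is the sponsor's.

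**Conclusion.** The concern holds. For the design as stated, the 90% is wrong by a factor of more than two. The chance of missing the target effect on the primary outcome is at least 58% with all 300 subjects evaluable (100 − 41.6) and at least 65% with 240 (100 − 34.6). The sample needed for 90% is more than three times the planned total.

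The conclusion rests on a two-arm 1:1 comparison, a binary success outcome, an odds ratio of 1.5 and a two-sided 5% level, all stated in the article. It needs no assumption about the control success rate. The detectable odds ratios do depend on it and are given for control rates of 20% to 50%.

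**What to change.** Correct the sample-size paragraph before results are reported:

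1. Confirm that an odds ratio, not a risk ratio, was intended.
2. State the assumed control success rate and its basis.
3. Recompute power for a binary 1:1 predictor.
4. Say that 300 is the number enrolled and whether the power figure refers to 300 or to 240 evaluable subjects.
5. State that a non-significant result does not exclude an odds ratio of 1.5.

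If 300 is kept, the text could read: *with 240 evaluable subjects and an assumed 40% success in the control group, the trial has 90% power for an odds ratio of about 2.35 and about 34% power for an odds ratio of 1.5*. The 40% is illustrative; the sponsor should supply its own figure.

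The cost is a rewritten paragraph with a less favourable figure and no change in enrolment. Keeping both the odds ratio of 1.5 and the 90% would instead require about 1,030 or more evaluable subjects.

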### Intervention

A group approach will be used. The intervention will be focused not only on cognitive enhancement, but also on several other aspects, such as advice and psycho-education about healthy lifestyle strategies as well as engagement in leisure activities. EG will be followed by a multidisciplinary team (i.e., psychologists, physicians, nurses, tango instructors and music therapist).

Multimodal intervention will consist in a 20-class syllabus of 180-min session, once a week, including 90 min of adapted tango in accordance to guidelines for physical activity in aging and literature [15], and, in the same session, further 90 min of comprehensive cognitive intervention for 6 months. The intervention will maximize social participation. Tango will be adapted for older adults with mild cognitive decline and possible mild balance and musculoskeletal impairment. Tango classes will be carried out in a ballroom dancing, led by two experienced and qualified Argentine instructors, with years of certified proficiency and experience in teaching adapted tango methods to elderly people. Classes will take into account the engagement of participants and feasibility. Each class will include about 25 subjects who will dance in pairs with other participants, including instructors, relatives and caregivers. Classes will begin with a phase of warm-up consisting of postural alignment and breathing. The main phase of dance will include enhancement exercises and addition of novel simple steps at each class with varied speeds and rhythms, individually and in pairs, focused on body awareness to educate subjects on prevention of falls, improving mobility, foot placement, whole body coordination, postural control, balance, self-confidence and attention to dance partner. In the last phase, participants can share their experience or ask questions. Possible adverse events will be tracked.

Cognitive intervention will include restorative and compensatory cognitive stimulation, learning mnemonics strategies and music therapy, and will be carried out by two trained psychologists and a music therapist. Intervention will use a metacognitive and a motivational approach applied to subjects with MCI, as described in previous studies [43, 44]. Participants will be also required to perform home exercises, which will include some cognitive stimulation exercises, assigned at the end of each class. Homework will be reviewed by the psychologist during the next class.

An example syllabus of classes is reported in Table 2.

**Table 2 Tab2:** Example syllabus of classes

Classes			
First class	Welcome to participants. Subjects can share their experience about cognitive impairment or ask questions.	75 min of psycho-education about healthy lifestyle aimed to prevention of dementia and other pathologies	90 min of dance. Explanation about the aim of adapted tango
Second class	Welcome to participants. Questions of participants.	75 min of psycho-education and health advice about the cognitive enhancement for prevention and management of cognitive disorders. Assignment of homework	90 min of adapted tango, as indicated in “Methodology”
Third class	Welcome to participants. Questions of participants. Revision of homework assigned the previous week.	75 min of cognitive stimulation aimed to learning of mnemonic strategies. Assignment of homework	90 min of adapted tango, as indicated in “Methodology”
Fourth class	Welcome to participants. Questions of participants. Revision of homework assigned the previous week.	75 min of music therapy. Assignment of homework	90 min of adapted tango, as indicated in “Methodology”

Possible adverse events, adherence to the study and participants’ attrition will be monitored by the principal investigator, adapted tango teachers and other staff members involved in the intervention.

To avoid bias effect of the intervention, GC will receive psycho-education and advice for healthy lifestyle as well as suggestions about the prevention of dementia once a month for 6 months. This group will receive the same clinical monitoring of the general health status, neuropsychological assessment, and cardiovascular parameters of EG. Moreover, they will be informed about the results and possible benefits of intervention, so they could have the possibility to start classes of tango therapy at the end of the study, if they so wish. Indeed, at the end of the study, we expect that this type of program will become a new service offered by IRCCS INRCA to elderly persons with an increased risk of cognitive decline.

